### **Assessment of Causality**

The investigator will use clinical judgment to determine the degree of certainty with which adverse event is attributed to drug treatment. Alternative causes, such as natural history of the underlying diseases, concomitant therapy, etc are to be considered taking into account the known pharmacology of the drug, any previous reactions, literature reports and relationship to time of drug ingestion or recurrence on re challenge. Causality will be assessed using the following categories; not related, unlikely, suspected (reasonable possibility) or probable. Patients with adverse events will be followed-up until the event disappears or the condition stabilizes.

### **Serious Adverse Events**

A serious adverse event will be defined as any event which is fatal, life threatening, disabling or incapacitating or results in hospitalization, prolonged hospital stay or is associated with congenital abnormality, cancer or overdose (either accidental or intentional). In addition, any experience which the investigator regards as serious or which suggests any significant hazard, contraindication, side effect or precaution that might be associated with the use of the drug will be reported as a serious event. Any serious adverse event occurring either during the study or within 30 days, or 5 half lives (whichever is longer), of receiving the last dose of study medication, is to be reported by telephone to the study monitor within 24 hours. This will be followed by a full written summary containing relevant hospital case records and autopsy reports where applicable.

As treatment is by parenteral injection, over dosage is not anticipated. However, in the event of over dosage (error of dosage calculation or administration) will be communicated to the study coordinator, [name], within 24 hours or as soon as possible thereafter. Details of any signs or symptoms and their management will be recorded in the CRF including details of any antidote(s)

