### **Need for new treatment options**

In eastern Africa, the first line treatment today in most endemic areas is antimonial therapy for 4 weeks sodium stibogluconate, (Pentostam® from GSK in Kenya or generic SSG from Albert David in Sudan and Ethiopia) used at 20 mg/kg/day for 28-30 days). Although the efficacy of this treatment is not yet compromised by resistance in this region (in contrast to Bihar – India), the painful daily injections, the need for four weeks of hospitalisation, the toxicity when using longer treatments, the low efficacy in HIV co-infected patients and the risk of inevitable drug resistance, as observed in India, make alternative options a necessity. Second line treatments are either toxic or prohibitively expensive.

In 2002-3, a combination of SSG and PM given for 17 days was used in an epidemic situation in Southern Sudan, with an initial cure rate of 97% (personal communication from [name], Médecins Sans Frontières). These findings were in line with previous published experience in the same area (Seaman et al, 1993) and experience in Kenya (Chunge et al, 1990). The proposed study aims to confirm these results in a randomized prospective comparative study.

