## **HYPOTHESIS**

That a combination course of SSG and PM (17 days) is similar in efficacy to either PM alone(21 days) or SSG alone (30 days) and that the shorter course combination (17 days) is not more toxic than PM or SSG alone.

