## **METHODOLOGY**

### **STUDY DESIGN**

This will be a multi-centre, prospective, open, parallel group, comparative trial of efficacy and safety of SSG alone given IM/IV (according to usual hospital practice) for 30 days versus paromomycin alone given IM for 21 days versus a combination of SSG and PM given for 17 days, in the treatment of patients suffering from VL in Ethiopia, Kenya and Sudan.

Patients who have clinical symptoms and a confirmed parasitological diagnosis of VL by splenic aspirate, lymph nodes aspirate or bone marrow aspirate (to be specified for each hospital site) and who have fulfilled the inclusion/exclusion criteria will be enrolled.

The primary endpoint will be cure rate at 6 months post treatment. Secondary endpoints will be cure rate at end of treatment (Day 31 for SSG, Day 22 for PM, Day 18 for PM + SSG) and at three months post treatment.

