## **ETHICAL CONSIDERATIONS**

The study protocol together with patient information and consent forms will be submitted to the local scientific and ethics committee and any other regional or national regulatory authorities as required in the three countries, Kenya, Sudan and Ethiopia, before the study starts and any patient receives study medication.

The patients who participate in this study will be hospitalized and under close monitoring. The invasive diagnostic methods used in the study are those used in

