## **FINAL VERSION LEAP 0104 31 JULY 2004 CONFIDENTIAL**

normal clinical practice when treating patients with VL. However, the frequency of testing might be increased depending on the patient's response to treatment.

Children will be included in this study because they represent more than 50% of VL cases in this region.

The effective treatment of VL benefits not only the individual patient but also the community by reducing the reservoir of infection for onward transmission by the sandfly vector. The evaluation of new and better treatments for VL, including shorter courses and combinations is anticipated to have a positive effect on development of parasite resistance and will reduce hospitalisation costs. If paromomycin is found to be efficacious and safe, it will be registered for the treatment of VL, providing a new alternative to treatments already available.

Patients will experience some pain while blood is drawn during venepuncture. The amount of blood to be drawn will be 10 mls before treatment and 7 mls at each subsequent visit, with a total of 42 mls (PM alone and a combination of PM and SSG), 49 mls (SSG alone) over the 6 months study period.

SSG has been extensively used in Sudan, Ethiopia and Kenya. Known adverse events include cardiac, muscle, joint and renal toxicity. PM has been used in clinical trials in Sudan and Kenya during the 1990's, and more recently in humanitarian emergency setting in Sudan. Known adverse events of the aminoglycosides include ototoxicity and renal toxicity.

Patients who are found to be HIV positive will be offered anti retroviral treatment at no cost in accordance with national guidelines for treatment.

A Data Safety and Monitoring Board (DSMB) will be set up to regularly review safety data.

Patients will be reimbursed for travel to and from the study site and will not receive any payment for trial participation. Any medication that is required during the trial period will be provided free of charge to the patient.

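### An event that is serious only because it leads to or lengthens a hospital stay can be an SAE in a shorter arm and not in a longer one, because all patients are inpatients and the expected stay differs by arm

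*Protocol*

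**What the plan says.** The Serious Adverse Events section of the protocol lists the criteria for seriousness. Besides death, they include an event that is "life threatening, disabling or incapacitating or results in hospitalization, prolonged hospital stay". The section does not say what a stay must be prolonged beyond, and it does not mention the admission that the study treatment itself requires. It also makes reportable "any experience which the investigator regards as serious", and it covers events "occurring either during the study or within 30 days, or 5 half lives (whichever is longer") of the last dose.

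Under Ethical Considerations the protocol states: "The patients who participate in this study will be hospitalized and under close monitoring". The courses last 30 days (SSG), 21 days (PM) and 17 days (combination). Study Design sets the end-of-treatment assessment at "Day 31 for SSG, Day 22 for PM, Day 18 for PM + SSG".

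No discharge day is given, but three places tie the stay to the course. Table 1 of treatment options describes antimonials as a 30-day treatment in hospital. The section on the need for new options cites "the need for four weeks of hospitalisation" as a drawback of SSG. Ethical Considerations expects that new treatments, including shorter courses, "will reduce hospitalisation costs".

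The Hypothesis section includes comparative safety: "the shorter course combination (17 days) is not more toxic than PM or SSG alone".

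**The concern.** A hospital criterion works the same way in every arm when patients start as outpatients or all have the same planned stay. Here neither holds. A patient already in hospital cannot be newly hospitalised by an event. A stay is prolonged only if the event outlasts the planned stay, which is shortest in the combination arm. Two patients with the same event on the same day, needing the same care, can then be classified differently because of the arm alone.

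The toxicity half of the hypothesis is at stake. SAE counts by arm are a natural summary for it, and the Data Safety and Monitoring Board that is to review safety data would see the same distortion. This cannot be left wholly to an analysis plan: the definition decides what is reported as serious at the time, and an event never classified as serious is hard to recover later.

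**Working it through.** **No plan figure to reproduce.** The protocol gives no SAE rate, so the check counts days.

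**Inputs**
- Planned last inpatient day T: 17 (combination), 21 (PM), 30 (SSG). This is inferred by equating the stay with the course.
- Onset day t, with L consecutive days of inpatient care from onset. L is an assumption, shown for 3, 7 and 14 days.
- The event meets no other seriousness criterion.

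**Rule.** Care runs from day t to day t + L − 1. The event qualifies through prolongation or readmission if t + L − 1 > T.

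**Two examples**
- Onset day 14, 7 days of care: care ends on day 14 + 7 − 1 = 20. This is past 17 but not past 21 or 30, so it is an SAE in the combination arm only.
- Onset day 20, 3 days of care: care ends on day 22. This is past 17 and 21 but not 30, so it is an SAE with the combination and with PM, but not with SSG.

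**Count.** With onset days 1 to W, the number of qualifying days is W − (T − L + 1). For L = 7 and W = 31:
- combination: 31 − (17 − 7 + 1) = 20
- PM: 31 − (21 − 7 + 1) = 16
- SSG: 31 − (30 − 7 + 1) = 7

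In the difference between two arms, W and L cancel, leaving the difference in T:
- combination v SSG: 30 − 17 = 13 discordant onset days
- PM v SSG: 30 − 21 = 9
- combination v PM: 21 − 17 = 4

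Every discordant day is an SAE in the shorter arm and not in the longer one. For L = 7, the discordant days for combination v SSG are 12 to 24.

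**Relative size.** The ratio does depend on W:

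| Days of care L | Window W | Combination | PM | SSG | Combination / SSG |
|---|---|---|---|---|---|
| 3 | 31 | 16 | 12 | 3 | 5.3 |
| 7 | 31 | 20 | 16 | 7 | 2.9 |
| 14 | 31 | 27 | 23 | 14 | 1.9 |
| 3 | 90 | 75 | 71 | 62 | 1.21 |
| 7 | 90 | 79 | 75 | 66 | 1.20 |
| 14 | 90 | 86 | 82 | 73 | 1.18 |

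The ratios assume that onset is uniform over the window and identical in all arms. The day differences of 13, 9 and 4 need only the inferred stays.

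**The case against.** The strongest reply is that the criteria are conventional and that the hospital criterion is only one of several. Fatal, life-threatening and disabling events qualify equally in every arm. So does anything the investigator regards as serious, whatever the length of stay. This stands as a limit: only events that qualify through the hospital criterion alone are affected. It does not remove the problem, because the investigator clause is discretionary in an open-label trial and does not make the arms comparable.

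Second, the discharge days are inferred. Days 18, 22 and 31 are assessment days, and a site could keep patients longer. That also stands, though the protocol's own argument for shorter courses rests on shorter stays.

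Third, a reader might infer that SAEs in the combination arm are inflated three- to five-fold. The documents do not support this. Those ratios come from ending the window on day 31, the SSG end-of-treatment day. SAE reporting covers the whole study, which runs to the 6-month visit, and over 90 days the ratio is about 1.2. Uniform onset is also doubtful after day 17, when combination patients are off drug: the protocol itself links paromomycin's ear and kidney toxicity to total dose and duration.

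Fourth, a reader might infer that ordinary adverse events are skewed the other way because SSG patients are observed for longer. The protocol collects all adverse events from consent, asks about side effects at each visit, and words its question to cover the time since the last assessment. It proposes no comparison restricted to the treatment period.

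Finally, no SAE count is a stated endpoint or test, and safety also rests on laboratory tests, urinalysis, ECG and audiometry. The distortion runs against the combination, so it would not by itself produce a false finding that the combination is no more toxic. It could suggest an excess that is not there.

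**Conclusion.** The point holds in limited form. Followed as written, the SAE definition lets the assigned arm decide whether an event that is serious only through the hospital criterion counts. The discordance is about 13 onset days for combination v SSG, 9 for PM v SSG and 4 for combination v PM, always against the shorter course. This assumes that patients leave hospital at the end of their course. The relative effect cannot be fixed from the protocol, which gives no event rates: under uniform and identical onset, with 7 days of care, it is 2.9-fold over 31 days and about 1.2-fold over 90. It is right to say that the same event can be classified differently by arm. It would go too far to say that it always is, or that SAE counts as a whole are distorted to that degree. The definition should be amended, because it bears on the safety half of the hypothesis and the change is small.

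**What to change.** Keep the conventional criteria and make two additions to the Serious Adverse Events section:

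1. State that the planned admission for study treatment is not itself an SAE.
2. State that an event which would by itself require inpatient care is recorded as serious, or flagged on the CRF, in every arm, whether or not the patient is already in hospital. This supplements the existing hospital criterion and does not replace it.

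Report the between-arm SAE comparison twice, with and without events that qualify only through the hospital criterion. This specification can sit in the analysis plan, provided that the CRF records which criterion was met.

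The cost is a short addition to the definition, one CRF item and one extra table. There are two drawbacks. There will be a few more SAE reports, mainly in the SSG and PM arms. The added item also asks unblinded investigators for a hypothetical judgement, which is why the observable criterion should stay beside it and both comparisons should be shown.

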## **FINAL VERSION LEAP 0104 31 JULY 2004 CONFIDENTIAL**

administered. As there are no specific antidotes available for the medications to be used in this study, patients will receive all supportive care needed at discretion of the treating physician and after consultation with the study coordinator above.

### **DATA COLLECTION, STORAGE AND ANALYSIS**

#### **Data Management**

In order to ensure data quality, a uniform hard copy i.e case report form (CRF) will be designed for use at all the sites. Data will then be sent to the coordinating site for data entry. It will be the responsibility of the investigator to ensure that the CRF is correctly completed to avoid unnecessary delays.

The software of choice will be EpiInfo 2003 which has an adequate electronic data capture (EDC) module especially for double entry. The data will be entered using pre-designed screens matching the data collection tool for ease of entry and validation. The entry program will also have in-built checks to minimize entry errors such as minimum and maximum, allowable values, legal values, jumps and values one must fill.

This exercise will be carried out by well-trained data entry personnel who will manage the data under the guidance of the biostatistician at the Centre for Clinical Research Centre of KEMRI.

#### **Analysis**

In the analytical approach intention to treat will be used. The aim is to estimate the difference in treatment outcomes for the three arms. The intention to treat analytical method will take care of events such as patient withdrawal from the trial, failure to comply with treatment, change in treatment and lost to follow-up.

There are two basic options:

Analyse final outcome only for those who complied perfectly with each treatment

Analyse data for all subjects in the groups to which they were randomized. This is referred to as 'Intention to treat' analysis or the 'pragmatic approach'.

The second option will be adopted, analysis will be carried out according to the original treatment assignment regardless of adherence to treatment or protocol.

There will be no exclusion of patients or events. Drop-outs will be checked to establish whether they were systematic or non-random. The analysis will, as much as possible stick to the protocol to avoid data dredging as part of post ad hoc analysis.

Note: Specific country analysis will be of little value because it lacks power. The data will have to be pooled for it to achieve the necessary power in the efficacy analysis.

Summary statistical measures to be computed

The summary statistics will include the  $\chi^2$  and risk ratios per arm for the overall efficacy comparison. The analysis and interpretation will heavily rely on confidence intervals of the cure rates among the three arms of the RCT. Other estimations to be made will be the calculation of the power finally achieved by the trial. This will be followed by the presentation of the results in terms of basic descriptive statistics and statistical diagrams. Finally multivariate analysis will be carried out to establish the socio-demographic factors associated with the main parameters.

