## **FINAL VERSION LEAP 0104 31 JULY 2004 CONFIDENTIAL**

time as consent is obtained for inclusion in the trial or at a later date according to hospital practice. HIV positive patients will not be excluded from the clinical trial. Subset analysis will be performed to assess any differences in response.

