### **Randomization in the Clinical Trial (RCT)**

The multi-country study adopted restricted randomization in a three-arm study per country. This approach prevents the potential pitfall/imbalance in study numbers that could have resulted if one used simple random sampling. In order to avoid manipulation of blocks of small sizes, blocks of size 15 will be used in randomization. This approach ensures that the study balances after the 15th patient. In the allocation of the drugs to the patients concealment will be used in order to minimize selection bias. Opaque envelopes will be numbered sequentially and then sealed. This process will be carried out at the coordinating centre at KEMRI.

[figure not shown]

Fig 1: The structure of the RCT

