### **Sample size Determination**

The sample size will be used to test the following statistical hypothesis as stipulated earlier:

**Hypothesis:** The three therapies differ by clinically relevant amounts

**Alternative Hypothesis:** The three therapies do not differ by clinically relevant amounts

A cure rate of 85% to 95% was used in the sample size calculation, where 85% represents the worst-case scenario and 95% the best outcome. The difference of these two proportions gives the size of the treatment effect sought in the randomized clinical trials.

This means that we are dealing with a dichotomous variable where the patients will be categorized as cured or not cured. A power of 90% and 5% level of significance are also required. The calculated sample size was adjusted for attrition and other covariates such as HIV/AIDS which was observed to be high in some of the participating countries.

Allocation adopted – uniform and equal allocation where  $\lambda = n_t/n_c = 1$

The sample size  $n = r * n_t$  [r is the number of active groups] which is calculated as follows:-

$$n_t [\text{per arm}] = k * [(p_1(1-p_1) + p_2(1-p_2))/(p_1-p_2)^2]$$

Where:

$n_t$  = sample size

$z_{\alpha/2}$  = the corresponding value to the 95% CI

$z_{\beta}$  = The corresponding value to power of 90%

$p_1$  = anticipated cure rate = 95%

$p_2$  = worst case scenario = 85%

$q_1 = 1 - p_1$

$q_2 = 1 - p_2$

where  $k = 10.5$  for power of 90%

For 90%

$$n_t \geq 10.5 [(0.85(0.15) + 0.95(0.05))/0.01] = 184$$

The sample size was adjusted to account for attrition rate due to loss to follow up, which is anticipated to be 15%. Thus the minimum sample size becomes  $n = 217$ .

HIV/AIDS was likely to be a covariate that could affect the primary variable-cure rate, especially in Ethiopia where the co-infection rate is estimated to be above 20%. This necessitated a further adjustment of the sample size for Ethiopia by 20% in order to be able to attribute the true treatment effect of the test drugs after controlling for HIV/AIDS. Thus the total for the three arms is 695.

The participating teams from Kenya, Ethiopia, Sudan and MSF were asked to specify the number of cases they could conveniently handle given the existing capacity and available infrastructure. This approach was used in absence of any other criteria. On the other hand some of the countries have very high case-load.

Table 1: Sample size per group

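### The stated efficacy comparison carries neither country, which restricts the randomisation, nor HIV status, for which Ethiopia's sample was enlarged; the pooled test stays valid but is slightly conservative

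*Protocol*

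**What the plan says.** **Randomisation (Protocol, Randomization in the Clinical Trial).** "The multi-country study adopted restricted randomization in a three-arm study per country", in blocks of 15.

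**Sample size (Protocol, Sample size Determination).** "A cure rate of 85% to 95% was used in the sample size calculation", and "A power of 90% and 5% level of significance are also required". Allocation to the three arms is equal. After an allowance for attrition, Ethiopia's sample is raised by 20% "in order to be able to attribute the true treatment effect of the test drugs after controlling for HIV/AIDS". The section names HIV as a likely covariate for cure rate and puts co-infection in Ethiopia above 20%.

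**Analysis (Protocol, Analysis).** The overall efficacy comparison uses chi-square and risk ratios, and interpretation rests mainly on confidence intervals of the arm cure rates. Country-specific analysis is set aside for lack of power: "The data will have to be pooled for it to achieve the necessary power in the efficacy analysis". The only model mentioned is the last step: "Finally multivariate analysis will be carried out to establish the socio-demographic factors associated with the main parameters".

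**HIV (Protocol, HIV-status and VCT).** Testing is voluntary and may follow after trial consent, according to hospital practice. HIV-positive patients are not excluded. "Subset analysis will be performed to assess any differences in response".

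**The concern.** Two design decisions have no counterpart in the stated efficacy comparison.

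- **Country.** Arms are balanced within country, but the comparison does not carry country. Lack of power is a good reason not to report three separate country results. It is no reason to drop country from the pooled comparison, because a stratified estimate uses every patient.
- **HIV.** Extra patients are justified by an HIV-controlled treatment effect, and no listed analysis produces one. The subset analysis asks whether response differs by HIV status, which is a different question. The closing model is aimed at socio-demographic factors.

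The protocol itself expects HIV to matter. Its review of disease distribution gives co-infection of up to 40% in the north-west Ethiopian focus and under 2% in the southern foci. Its section on the need for new treatments cites low antimonial efficacy in co-infected patients.

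At stake are some precision, protection against a chance HIV imbalance between arms, and the reason given for part of the recruitment. Precision matters here because the trial's hypothesis is that the combination is similar in efficacy to either drug alone, and a needlessly wide interval works against showing that.

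**Working it through.** **1. The protocol's own figures reproduce.**

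- Per arm: 10.5 × (0.85×0.15 + 0.95×0.05) / 0.10² = 10.5 × 0.175 / 0.01 = 183.75, so 184.
- Attrition of 15%: 184 / 0.85 = 216.5, so 217. Three arms: 651.
- Ethiopia plus 20%, taking Ethiopia as one third (217; my assumption): 651 + 0.2×217 = 694.4, so 695. The addition is 695 − 651 = 44 patients.
- Team table: 60 + 150 + 225 + 150 + 120 = 705, or 235 per arm. Ethiopia holds 150 + 120 = 270 (38%).

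**2. Assumptions for the size of the effect.** The protocol gives no cure rates by country or HIV status. I assume HIV prevalence of 40% in Gondar, 2% in Southern Ethiopia and 0 elsewhere, with cure of 95% without HIV and 50%, 60% or 70% with it. Expected HIV-positive patients: 0.40×150 + 0.02×120 = 62.4, about 21 per arm. That is 62.4/270 = 23% of Ethiopian patients, in line with the protocol's figure of above 20%.

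**3. Stratified against crude variance.** With strata balanced across arms, the ratio is Σ w·p(1−p) / [p̄(1−p̄)], where w is the stratum's share of patients, p its cure rate and p̄ the overall rate. The excess in the crude standard error is 1/√ratio − 1.

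Example, HIV-positive cure 50%:

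- p̄ = 0.95 − (62.4/705)×0.45 = 0.9102, so the crude variance term is 0.9102×0.0898 = 0.0818.
- Country strata: cure in Ethiopia is 0.95 − 0.231×0.45 = 0.846. The term is (435×0.95×0.05 + 270×0.846×0.154)/705 = 0.0792, ratio 0.97.
- HIV strata: 0.9115×0.0475 + 0.0885×0.25 = 0.0654, ratio 0.80.

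| HIV-positive cure | Crude SE excess v country | v team | v HIV |
|---|---|---|---|
| 50% | 1.6% | 3.4% | 11.8% |
| 60% | 1.1% | 2.2% | 7.4% |
| 70% | 0.6% | 1.3% | 4.0% |

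In points at 235 per arm and 50% cure, the half-width 1.96×√(2×variance term/235) is 5.17 crude, 5.09 by country and 4.62 by HIV.

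**4. Error rates by simulation.** 200,000 runs; 20, 125 and 90 patients per arm in Kenya, Sudan and Ethiopia; allocation balanced within country; no true difference. All country cure rates are assumed.

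| Cure, Kenya/Sudan/Ethiopia | Rejection, pooled | Rejection, stratified | Coverage, pooled 95% CI |
|---|---|---|---|
| 90/90/90 | 5.1% | 5.0% | 94.9% |
| 92/92/87 | 5.0% | 5.0% | 95.0% |
| 95/93/80 | 4.6% | 4.9% | 95.4% |
| 95/95/70 | 3.6% | 5.0% | 96.2% |
| 97/95/55 | 2.5% | 4.9% | 97.4% |

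Power for 85% against 95% was 96-97% pooled and 96-98% stratified.

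**5. Can the HIV subset stand in for adjustment?** With 21 per arm the half-width for a difference is 1.96×√(2p(1−p)/21): 30 points at p = 0.5 and 28 at p = 0.7. It cannot.

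**6. Chance HIV imbalance.** With teams balanced at 50 (Gondar) and 40 (Southern) per arm, the SD of the difference in HIV-positive counts between two arms is √(2×50×0.24 + 2×40×0.0196) = 5.1. Two SDs are about 10 patients, or 10.1/235 = 4.3% of an arm. Multiplied by a cure deficit of 25 to 45 points, this moves the crude difference by about 1 to 2 points, against a design difference of 10.

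**The case against.** The strongest reply is that nothing here is invalid. That stands. Restricting allocation by country balances the arms whatever the analysis, and leaving country out can only make the pooled interval conservative. HIV is not a randomisation factor, so omitting it costs precision and does not bias the test. A reader might infer that the error bars are wrong or that false-positive risk rises; the calculations show the reverse, and the country effect is negligible unless country cure rates differ by more than about 15 points.

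A reader might also infer that both design features go unused. That is too strong: the restriction does its balancing work, and an HIV subset analysis is planned.

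It can further be said that pooling does not exclude stratification, that the list of statistics is not worded as exhaustive, and that covariates are commonly left to a statistical analysis plan. This is fair as to model details. It does not remove the mismatch inside the protocol, which justifies recruitment by an HIV-controlled effect, names its efficacy measures and its one model without HIV, and says the analysis will keep to the protocol as far as possible.

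Finally, the 4-12% figure assumes HIV status is known for everyone, and testing is voluntary. That also stands; the real gain would be smaller. Crossing five teams with three HIV categories would give 15 strata, too sparse with Kenya at 20 per arm, so a simpler adjustment is needed.

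**Conclusion.** The point holds as an inconsistency between design and analysis, with a modest loss of precision. The stated efficacy comparison carries neither the randomisation stratum nor the covariate for which about 44 patients were added, and the planned subset analysis cannot deliver the HIV-controlled effect.

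The primary comparison is not threatened. Type I error is not inflated, and in the country simulations the power lost is about 1 point or less. What can be gained is about 1-2% of the standard error from country and at most 4-12% from HIV. These sizes rest on assumed HIV prevalences and cure rates, and the 44 on Ethiopia being one third of the sample. The mismatch between sections does not depend on those assumptions. It is worth correcting because the correction costs almost nothing.

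**What to change.** In the Analysis section:

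1. Keep the data pooled, and make the main comparison a Mantel-Haenszel risk difference with 95% confidence interval, stratified by country. Keep the crude chi-square as supportive.
2. Add one pre-specified HIV-adjusted treatment estimate, for example a regression with country and HIV status in three categories: positive, negative, and not tested by the start of treatment. Fixing status at the start of treatment stops the grouping from depending on tests done after response is known, and gives untested patients a place. Alternatively, withdraw the HIV rationale for enlarging Ethiopia's sample.

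Cost: a few sentences and slightly more analysis work, with no change in sample size. The gain from HIV adjustment shrinks if many patients are untested by the start of treatment.
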